## Introduction

### Background and rationale {6a}

Family Integrated Care (FICare) promotes the active participation of family members in providing specialised care to their sick newborn baby admitted to the neonatal intensive care unit (NICU). This change in paradigm in neonatal care, initially developed and implemented at Mount Sinai Hospital in Toronto in the stable preterm infant, has shown promising results in improving health outcomes in this population. The first pilot study conducted by O’Brien et al. demonstrated that parental involvement in direct care led to better weight gain, increased breastfeeding rates, and reduced stress and anxiety levels among parents of preterm infants [1].

These findings were further supported in a cluster-randomised controlled trial [2], as well as in subsequent studies highlighting the positive effects of the model in accelerating maturation processes [3] (earlier full enteral nutrition [3, 4]) shorter duration of mechanical ventilation and hospital length of stay [5–9], decreased rates of late-onset sepsis [5, 6], and improvements in neurobehaviour at 18 months [7]. Recently, Moreno-Sanz [8] described the successful adaptation and implementation of FICare policies also in the unstable, critically ill premature infant and the high-risk neonate with complex medical or surgical conditions, suggesting the potential for generalising the FICare model as the standard of care in NICUs.

However, the FICare model has only been tested up to now in high-income, developed countries. FICare relies on structured professional and caregiver training and parental physical and psychological support, which implies the provision of resources. Yet, the scalability of the model to overcome social-cultural barriers and cost-effectiveness analysis has not been tested.

RISEinFAMILY is an international consortium that has been designed for adapting and implementing FICare in different regions of Europe and Africa. The expansion of FICare to other NICUs and countries necessitates further research to identify potential constraints that may limit its adoption, particularly in low- and middle-income countries with different sociocultural contexts. Understanding these barriers and developing strategies to address them will be crucial in realising the full potential of FICare and ensuring its successful implementation globally.

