### Outcomes {12}

The study’s primary outcomes are as follows: (a) RISEinFAMILY implementation: proportion of families completing basic and advanced training levels (observed vs expected), average time to complete basic and advanced training levels (observed vs expected) and average time of kangaroo care per day (hours); (b) short-term health infant’s outcomes: proportion of high-risk infants achieving and maintaining adequate growth patterns during NICU admission, defined according to Patel’s method [10, 11].

The study’s secondary outcomes are as follows: reported adverse event rate per 1000 patients/day, feeding patterns and major morbidities at 36 weeks postmenstrual age (PMA) or discharge, nosocomial infection [12], necrotising enterocolitis (Bell’s > stage 2), moderate-severe brain injury (worst cranial ultrasound) [13], parental needs, empowerment and psychological health (stress [14], anxiety and depression [15, 16], self-efficacy [17], bonding [18], resilience [19]), professional’s self-care and satisfaction (anxiety and depression [15], burnout [20], post-traumatic stress [21], work and well-being [20]).

The study’s exploratory outcomes are as follows: economic impact (level of post-implementation utilisation of FICare, resources and costs associated with FICare implementation, cost-effectiveness estimates compared to the current care, expected value of current implementation and expected value of perfect implementation); mid-term infant’s general health (growth pattern during the first 12 months from birth, use of health system facilities after discharge); long-term neurodevelopment (survival without neurodevelopmental disabilities).

Specific items and test batteries are stated in Additional file 1.

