## Data collection and management

### Plans for assessment and collection of outcomes {18a}

Data will be collected by researchers at participating hospitals and stored anonymously in a digital database (Research Electronic Data Capture; REDcap). Data will be stored in accordance with guidelines issued by the Spanish Data Protection Agency. Independent monitors will perform source data verification and assess the performance of trial procedures at least once a year at each site. FIBHULP will be responsible for the data management and storage of the study data. The veracity of the data will be ensured through the training of the professionals in charge of the REDCap database. In addition, a database user manual has been included in the study folder accessible to all researchers.

There will be several time points for data entry: screening, enrolment, weekly visit up to discharge to home or transfer to a non-FICare centre, short-term clinical outcome assessment, mid-term clinical outcome assessment and long-term clinical outcome assessment. If the infant in the meantime has been discharged to a step-down unit, data should be sought from the specific unit. If this is not possible, data should be used until the date of discharge to the step-down unit.

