## Statistical methods

### Statistical methods for primary and secondary outcomes {20a}

The primary analysis will be conducted in the intention-to-treat (ITT) population including all enrolled patient-family dyads who received at least one task training according to protocol procedures.

Descriptive statistics will be recorded for each group with mean, median and standard deviation for numerical variables and absolute and relative frequencies for categorical variables. 95% confidence intervals (CIs) will be provided. Comparisons between control and intervention groups will be performed using chi-square tests for categorical variables, analysis of variance for normally distributed continuous variables, and Mann–Whitney or Kruskal–Wallis tests for non-normally distributed continuous variables. Through a mixed-methods research approach and techniques both quantitative and qualitative, the following impacts will be evaluated: (a) effect of intervention: the control and the intervention group dataset from the non-FICare-experienced centres will be compared; (b) effect of “expertise” on outcomes: comparisons will be conducted between datasets from already trained FICare centres and those from the non-FICare-experienced centres.

Socio-economic sustainability: Health economics analysis based on the value of implementation framework will be conducted to assess the cost-effectiveness of RISEinFAMILY implementation strategies. The difference between the total net benefit of perfect adoption and the total net benefit of current implementation will generate the expected value of perfect implementation (positive values would characterise cost-effective implementation strategies). The analysis will also allow identifying differences in delivering RISEinFAMILY in different countries/health care settings.

Psychological assessment of experiences collected by either the NICUs staff and the families enrolled in the pilots will be conducted. Gender differences will be explored in relation to socioeconomic and cultural background.

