For our primary hypothesis, we will compare infant standardised weight gain velocity between the two groups over the 4-week study period using generalised linear mixed modelling (GLMM). For our primary outcome, we will compare infant standardised weight gain between the two groups over the study period defined as the change in Patel’s growth pattern measured weekly from enrolment until day 28 post-enrolment, testing an interaction term between group and post-baseline weight measurements. We will adjust for additional covariates using a hybrid approach, forcing in known confounders of gestational age and study site and using backward stepwise selection to retain covariates that contributed *p* < 0.1 to the final model from potential confounders. Additionally, we will conduct sensitivity analyses by adding in weight measured at discharge.

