### Methods for additional analyses (e.g. subgroup analyses) {20b}

Important prognostic variables are centre, sex and gestational age, or main neonatal diagnosis. These will be used as additional independent variables in key secondary logistic regression models for secondary subgroup analysis.

Further subgroup analysis will be conducted in line with the primary analysis, where the endpoint is dichotomous. For continuous endpoints, similar modelling strategies will be used, but instead of logistic regression linear regression models will be used.

The cost-effectiveness analysis of RISEinFAMILY implementation will be carried out using recommended methods [35, 36]. A decision-analytical [37] will be developed and populated with costs and effectiveness data from the pilot studies. For each RISEinFAMILY implementation site, the cost-effectiveness of the intervention will be estimated. The cost-effectiveness and the value of implementation analyses will be conducted for the seven neonatal units involved in the study. The mean net monetary benefit per participant will be calculated using the health care system willingness-to-pay threshold corresponding to the current cost of neonatal care in the NICU.

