### Adverse event reporting and harms {22}

Considering the nature of the intervention and the characteristics of the patients who may present complications intrinsically to their biological or medical condition, serious adverse events will not be individually reported but will be part of the data collected as part of the assessment of benefits and harms.

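### The adverse event outcome is a rate over patient-days, but the tests stated for secondary outcomes do not model exposure time or repeated events, so false positives can be inflated if length of stay differs or events cluster within infants

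*Protocol article*

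**What the plan says.** Outcomes {12} of the protocol article lists "reported adverse event rate per 1000 patients/day" first among the secondary outcomes. It does not say how the rate is formed for testing: any event, event count, pooled rate or rate per infant.

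Statistical methods for primary and secondary outcomes {20a} then states: "Comparisons between control and intervention groups will be performed using chi-square tests for categorical variables", with "analysis of variance for normally distributed continuous variables, and Mann–Whitney or Kruskal–Wallis tests for non-normally distributed continuous variables". The mixed model in the same section is tied to weight gain: "we will compare infant standardised weight gain velocity between the two groups over the 4-week study period using generalised linear mixed modelling (GLMM"). Methods for additional analyses {20b} adds logistic models for dichotomous endpoints; for continuous ones, "instead of logistic regression linear regression models will be used". No count model and no person-time method is named.

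Three other statements bear on the point:
- Exposure differs between infants. Plans for assessment and collection of outcomes {18a} sets data entry at a "weekly visit up to discharge to home or transfer to a non-FICare centre".
- Background and rationale {6a} cites earlier studies of the care model that found "shorter duration of mechanical ventilation and hospital length of stay". It gives no size.
- Under Adverse event reporting and harms {22}, "serious adverse events will not be individually reported but will be part of the data collected as part of the assessment of benefits and harms".

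**The concern.** A rate over patient-days has two features that the listed tests do not handle: infants are observed for different lengths of time, and one infant can have several events.

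If the intervention shortens stay, intervention infants have fewer days in which an event can occur. A test that drops the denominator then reads shorter stay as fewer adverse events. The same mechanism can hide harm. As an illustration, 20 events per 1000 patient-days over 40 days and 25 per 1000 over 32 days both give 0.80 expected events per infant (0.020 × 40 = 0.025 × 32), although the second rate is 25% higher.

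The outcome feeds the assessment of benefits and harms of a model in which parents carry out specialised care. The protocol plans no interim analysis and no data safety monitoring board, so the end-of-trial comparison should be one that can be interpreted.

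**Working it through.** **1. The plan's own figure.** There is none for this outcome. The protocol gives no adverse event rate, no repeat-event frequency and no length of stay; its sample size concerns weight gain. Everything numerical below rests on assumptions.

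**2. Which test the stated rule selects.** Analysis of variance is reserved for normally distributed variables. With low event rates many infants have a rate of exactly zero and the rest have a right tail. In simulated infant rates a normality test rejected in essentially every trial. The rule therefore leads to a rank test if the rate is treated as continuous, or to a chi-square if it is reduced to any event versus none.

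**3. Why the any-event chi-square goes wrong, by formula.** Assumptions: a true rate of 20 per 1000 patient-days in both groups (λ = 0.02 per day); stay = 7 days plus a gamma variable with coefficient of variation 0.6, so shape s = 1/0.36 = 2.78 and scale θ = (mean stay − 7)/s; no extra variation between infants; 230 infants per group. The last figure is an inference: 552 = 46 × 12, read as 5 sites × 2 phases + 2 sites × 1, so 5 × 46 = 230 per phase at sites 1-5.

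P(any event) = 1 − exp(−7λ) × (1 + λθ)^(−s)

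- Mean stay 40 days: θ = 33/2.78 = 11.88, P = 0.519.
- Mean stay 32 days: θ = 25/2.78 = 9.00, P = 0.451.
- Difference 0.068; SE = √(2 × 0.485 × 0.515/230) = 0.0466; expected z = 1.46.
- P(|Z| > 1.96) with mean 1.46 is about 0.31, against a nominal 0.05.

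The simulation below gave 0.300 for this setting.

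**4. Simulation.** Equal true rates in both groups; 230 versus 230 infants; 5, 20 or 50 events per 1000 patient-days; with and without a gamma frailty of variance 1 (infants differing in risk); control stay 40 days; no clustering by site; 2,000 runs per setting. Type I error at nominal 0.05:

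| Test | Stay 40 vs 40 | 40 vs 36 | 40 vs 32 |
|---|---|---|---|
| Chi-square, any event | 0.048-0.054 | 0.065-0.108 | 0.120-0.320 |
| Rank test, infant rate | 0.046-0.054 | 0.052-0.063 | 0.061-0.126 |
| Chi-square, pooled events over days, no frailty | 0.043-0.059 | 0.047-0.068 | 0.040-0.062 |
| Chi-square, pooled events over days, frailty | 0.083-0.316 | 0.082-0.294 | 0.071-0.280 |
| ANOVA, infant rate | 0.046-0.058 | 0.046-0.058 | 0.043-0.060 |
| Rate ratio with person-time, robust variance | 0.042-0.056 | 0.044-0.060 | 0.039-0.064 |

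With an assumed stay of 45 versus 36 days (also 20% shorter) and rates of 5 to 40 per 1000, the figures are about 10-30% for the any-event chi-square and 4-12% for the rank test, against 4-7% for the person-time rate ratio. The upper end for the any-event test belongs to equal groups. With 96 versus 288 infants it was 11-19%.

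**5. Reading the table.** The any-event test and the rank test depend on a difference in stay. The rank test is affected because a shorter stay gives more infants with a rate of zero and larger non-zero rates in the others, so the two distributions differ although the true rates are equal. The pooled chi-square depends instead on events clustering within infants, and is inflated even at equal stay.

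**The case against.** The strongest reply has four parts.

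- **One listed test holds its level.** Analysis of variance on infant rates divides by exposure, counts every event, and kept 3-6% throughout. This stands, and it rules out saying that no listed test could be valid. It does not rescue the plan: the protocol allows this test only for normally distributed variables, and infant rates will not be. It would also compare unweighted means of infant rates, which is not events over patient-days.
- **The inflation depends on inputs that the protocol does not give.** This stands. At equal stay the any-event and rank tests are at about 5%; at 36 versus 40 days the rank test is still at 5.2-6.3%. The pooled chi-square is only one possible reading, since the protocol assigns chi-square to categorical variables and nowhere says that patient-days will be tabulated.
- **An article may leave the model for one secondary outcome to the full analysis plan.** This would be decisive if the article were silent. It is not: it states a set of tests under a heading that covers secondary outcomes, confines the mixed model to weight gain, and adds only logistic and linear regression.
- **Site and calendar terms answer a different problem.** That is fair. The simulation included neither clustering nor time trend. The terms belong in the model because of the stepped design, not because of the figures above.

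A reader might also infer that this is the trial's main safety comparison and that its error rate is wrong as it stands. The documents support neither. The rate is one of several secondary outcomes, beside nosocomial infection, necrotising enterocolitis, brain injury and major morbidities, and the error rate is wrong only under conditions not yet known.

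**Conclusion.** The point holds as a mismatch between outcome and method. The outcome is an event rate over patient time; the stated tests model neither exposure nor repeated events, and the protocol's own normality rule leads away from the one listed test that kept its level.

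The consequence is conditional. If stay is about 20% shorter under the intervention (45 versus 36 days, assumed), equal true rates would be declared different in about 10-30% of trials by the any-event chi-square and 4-12% by the rank test. If stay is equal, both are at about 5%. A pooled chi-square, if it were used, would reach roughly 7-32% when infants differ in risk with an assumed frailty variance of 1. The direction of any difference in stay is suggested by the protocol's background; its size, the event rates and the clustering of events are not in the documents. The primary analysis and the sample size are not affected.

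**What to change.** In Statistical methods {20a}, state that the adverse event rate is analysed with a negative binomial (or overdispersed Poisson) model: event count per infant as response, log patient-days as offset, and terms for group, site and calendar period, reported as a rate ratio with 95% CI. In Outcomes {12}, write the unit as per 1000 patient-days.

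The cost is one sentence and one extra model for one outcome. Adverse events and dates are already scheduled in the activity table, so nothing new has to be collected.

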#### Questionnaires for parents

Abbreviated Parental Stressor Scale for Pediatric Intensive Care Unit (A-PSS:PICU) [22]: This scale, based on the PSS:PICU [14] includes 7 items to assess parental stress caused by the PICU environment. It has two factors (stress due to the child’s condition and stress related to PICU’s staff) and adequate internal consistency (*α* = 0.80). In this article, we have adapted the items to the NICU context.

Generalized Anxiety Disorder (GAD-7) questionnaire [23]: This is a seven-item questionnaire designed to assess the patient’s anxiety symptoms during the previous 2 weeks. It showed excellent internal consistency (*α* = 0.92) and test–retest reliability (intraclass correlation = 0.83). At a cut point of 10 showed the greatest sensitivity and specificity.

Edinburgh Postnatal Depression Scale (EDPS) [24]: This is a 10-item scale to measure depressive symptoms during the perinatal period. It showed excellent internal consistency (*α* = 0.91) and test–retest reliability (Spearman’s rho rank correlation = 0.90). The cutoff score of ≥ 13 indicates an elevated risk of depression.

The Perceived Maternal Parenting Self-Efficacy (PMP S-E) [17]: This is a 20-item questionnaire to measure maternal parenting self-efficacy, especially of hospitalised preterm neonates. It showed excellent internal consistency (*α* = 0.91) and test–retest reliability (Spearman’s rho rank correlation = 0.96).

The Postpartum Bonding Questionnaire (PBQ) [18]: It comprises 25 items with a 5-point Likert-type response scale. It measures the presence of bonding difficulties and has four subscales: affected bonding, rejection and hatred, anxiety about baby care, and risk of abuse. It provides a total score of the quality of bonding. It showed excellent internal consistency (*α* = 0.90) and test–retest reliability for the total scale (Spearman’s rho rank correlation = 0.96), and its subscales (Spearman’s rho rank correlation ranging from 0.77 to 0.95).

Brief Resilience Scale (BRS) [25] is a 6-item self-report scale that was designed to assess resilience as the ability to bounce back from stress. It has proved adequate reliability, shown adequate internal consistency (*α* ranging from 0.80 to 0.90) and test–retest reliability (*r* = 0.62–0.69) and validity.

Perceived social support scale: This is an ad hoc questionnaire designed to measure the degree to which parents were satisfied with the social support they were receiving now from their partner, family, friends and other close people different from family and healthcare staff.

Posttraumatic Stress Disorder-8 (PTSD-8) inventory [21] is an 8-item scale for screening for probable PTSD. The scale originates from the Harvard Trauma Questionnaire (HTQ) [26]. It consists of eight items rated on a 4-point severity scale. Positive screening requires a concurrent rating of at least one item from each symptom cluster (intrusion, avoidance, hypervigilance) with a score of three or higher. Its scores have shown adequate internal consistency (*α* = 0.83–0.85).

The 9-item Shared Decision Making Questionnaire (SDM-Q-9) [27] is a 9-item measure of the decisional process in medical encounters from the patients’ perspective. It has good reliability (*α* = 0.94) and high face and structural validity.

Posttraumatic Growth Inventory Short Form (PTGI-SF) [28] is based on the 21-item original version by Tedeschi and Calhoun [29], designed to measure the positive legacy of trauma. The PTGI-SF contains 10 items to measure five domains: greater appreciation of life, improved relationships with others, greater personal strength, recognition of new possibilities in one’s life course and spiritual or religious growth. It has shown adequate internal consistency (*α* ranging from 0.84 to 0.90) and validity. In order to make sure that the PTG that parents reported was a consequence to their child’s admission to the NICU; instead of asking about responses “as a result of my crisis”, we asked about responses “result of your child’s admission to the NICU”.

#### Questionnaires for healthcare professionals

The Four-Item Patient Health: PHQ-4 [15] is a valid ultra-brief tool for detecting both anxiety and depressive disorders. It includes two items that measure depression used in the PHQ-8 and two items that measure anxiety used in the 7-item Generalised Anxiety Disorder (GAD-7) scale. Each item is rated on a 4-point Likert scale. The PHQ-4 sum score is classified as none (0–2), mild (3–5), moderate (6–8) and severe (9–12) symptoms of general/unspecific anxiety and depression. Its scores have shown adequate construct and factorial validity.

Perception About Parental Participation: This is an ad hoc questionnaire designed for the purpose of this study. It includes 12 items on a 6-point Likert scale to measure healthcare workers’ perception about parental participation in the NICU. It measured to which degree professionals considered that (1) parental presence during medical procedures, (2) parental presence during medical rounds and decision-making processes, (3) open-door policies in the NICU, and (4) parental participation in their children’s care was beneficial for parents, the baby, and professionals.

Maslach Burnout Inventory (MBI) [30] is a 22-item questionnaire that assesses the frequency of occurrence of different feelings in relation to their job in the last week in a 7-point Likert scale. It contains three dimensions: emotional exhaustion (EE), depersonalisation (DP) and personal achievement (PA). A meta-analysis has shown an average internal consistency (Cronbach’s *α*) of 0.88, 0.71, and 0.78, respectively for each dimension [31]. Cutoff scores for EE are between 15 and 24 (the score is low if it is below 15 and high if it is up to 24), for DP between 4 and 9 and for PA between 33 and 39.

UNWES-9 Work & Well-being Survey (UWES) [32] is a 9-item questionnaire to measure work engagement. It includes three dimensions to measure vigour, dedication, and absorption. It has shown adequate factorial validity and internal consistency (Cronbach’s *α* for the total scale between 0.85 and 0.92).

9-item Shared Decision Making Questionnaire-version for physicians (SDM-Q-Doc 9 items) [33]: This is a 9-item measure of the decisional process in medical encounters from the physicians’ perspective. It has shown adequate internal consistency (Cronbach’s *α* of 0.88). Factor analysis confirmed a one-dimensional structure.

